# Exploratory randomised trial of face-to-face and mobile phone counselling against usual care for tobacco cessation in Indian primary care: a randomised controlled trial protocol for project CERTAIN

**DOI:** 10.1136/bmjopen-2021-048628

**Published:** 2022-01-06

**Keywords:** protocols & guidelines, primary care, qualitative research, public health

## Abstract

**Introduction:**

Despite widespread use of smokeless tobacco products by people within the Indian subcontinent, there is little awareness among Indians of its health hazards when compared with smoked tobacco. We hypothesise that mobile phone counselling will be feasible and effective for smokeless tobacco cessation intervention in India. This paper presents the protocol of the development and conduct of an exploratory trial before progression to a full randomised controlled trial.

**Methods and analysis:**

An exploratory randomised controlled trial will be conducted in urban primary health centres in the state of Odisha, India. A total of 250 smokeless tobacco users will be recruited to the study (125 in each arm). Participants in the intervention arm will receive routine care together with a face-to-face counselling intervention followed by advice and reminder mobile messages. The control arm will receive routine care, delivered by a primary care physician based on ‘Ask’ and ‘Advice’. All participants will be followed up for 3 months from the first counselling session. The primary outcome of this trial is to assess the feasibility to carry out a full randomised controlled trial.

**Ethics and dissemination:**

Ethical approvals were obtained from the Institutional Ethics Committee of Public Health Foundation of India, Health Ministry’s Screening Committee, Odisha State Ethics Board and also from University College London Research Ethics Committee, UK. The study findings will be published in a peer-reviewed scientific journal.

**Trial registration number:**

CTRI/2019/05/019484.

Strengths and limitations of this studyEvidence on the effectiveness of smokeless tobacco (SLT) cessation intervention in primary care is scarce. The results of this study will inform on the feasibility of conducting an effectiveness trial in the future.Randomisation with allocation concealment, blinded assessment of outcome measures and registration of the protocol in the trial registry will minimise potential bias.Providing training to health professionals will lead to an improved understanding of the delivery of low-cost tobacco cessation interventions in primary care.The primary care physicians may get unmasked to the allocation of the participants during the course of the trial as the participants visiting the urban primary health centres may reveal the information to the physicians. There is a chance of biased results if physicians may deliver repeated face-to-face counselling services.The inclusion criteria include SLT users having a mobile phone, this may exclude a section of the SLT users who do not have a personal mobile phone like very poor or the elderly who do not use a mobile phone.

## Introduction

Tobacco use is responsible for almost eight million deaths each year or a death every 6 seconds.^1 2^ About 80% of 1.3 billion tobacco consumers across the globe live in low and middle-income countries (LMICs).^1^ In LMICs like India, the tobacco problem is complex as the country has a diverse population with a mixture of cultures, religions and practices. The majority of the tobacco users in India use a variety of tobacco products—combustible, non-combustible or both. As per the Global Adult Tobacco Survey 2 (GATS 2), 28.6% of the adult population in India consumes tobacco (10.7% of smoking and 21.4% of smokeless), making it the second-largest consumer in the world.^3^

Widespread use of smokeless tobacco (SLT) products occurs in countries such as in India and Bangladesh accounting for 232 of 248 million SLT users worldwide (i.e., from 21 countries).^4^ SLT products such as *tambaaku*, *gurkha*, *zarda*, *khaini*, *mawa* and *pan masala* are widely used in many states in India as SLT consumption is culturally accepted and is considered common practice.^5^ In India, SLT use is double that of combustible tobacco, making it the single most common form of tobacco used by men and women (29.6% and 12.8%, respectively).^5^ According to GATS 2 survey, the state of Odisha was one where the largest proportion of adults consumed SLT products (43%) compared with the national average (21.4%).^6^ Despite strong evidence of SLT^7^ on cancer of the oral cavity, pharynx, oesophagus and also responsible for a large proportion of tobacco-related cancers in India, there is a misconception that SLT is relatively harmless.^8^

Primary care health professionals, the first contact for patients accessing help, play a key role in the health education of the hazards of tobacco. They are best placed to counsel against tobacco use and promote cessation. Studies on brief interventions by healthcare providers are effective in motivating tobacco users to quit tobacco.^9 10^ A systematic review on SLT cessation intervention from both high-income countries (HICs) and LMICs showed that behavioural interventions are effective in achieving cessation.^11^ However, the overburdened primary care physicians in India have limited time for counselling,^2 12 13^ and it is also difficult to get users to attend follow-up visits as journeys to primary care clinics would incur a loss of income.^12^

In India, mobile phones are widely used in both rural and urban settings. India with 1173.7 million (98.2%) mobile phone users is the second-largest user base in the world.^14^ Mobile phone subscribers in India increased from 1187 million in June 2019 to 1195.2 million by September 2019.^14^ A meta-analysis of 104 studies including randomised trials and quasi randomised trials on the effectiveness of telephone counselling for smoking tobacco cessation showed significant but modest effect sizes in HICs.^15^ Effectiveness increases with treatment intensity.^16^ A review of 26 trials on smoking cessation demonstrated that automated text messaging interventions were more effective than minimal smoking cessation support (RR 1.54, 95% CI 1.19 to 2.00; I^2^=71%; 13 studies) and text messaging added to other smoking cessation interventions was more effective than other individual smoking cessation interventions (RR 1.59, 95% CI 1.09 to 2.33; I^2^=0%, four studies).^17^ Another meta-analysis of 13 trials reported smoking quit rates with text messaging intervention were 35% higher than quit rates for controls (OR=1.35, 95% CI 1.23 to 1.49).^18^ Other reviews of studies from HICs suggest that such interventions can increase the chance of quitting smoking tobacco from 39% to 80%.^19 20^ Studies on SLT cessation that included randomised controlled trials conducted in HICs as well as some LMICs showed that behavioural cessation interventions led to quit rates between 9% and 51.5% at 6 months.^11 21^ There are, however, little data on the efficacy and effectiveness of such intervention combined with mobile phone-based counselling in LMIC like India. Improved participation in tobacco cessation programmes through the use of mobile phone technology can have a substantial impact on a population at risk even with a small effect size.^22^

There is an urgent need to test the effectiveness of the use of mobile phone messages for SLT cessation in the Indian primary care setting.^23^ We hypothesise that a face-to-face intervention offered by a tobacco counsellor together with low-cost mobile-based counselling has the potential to deliver a high-quality cessation intervention to SLT users. Prior to that, we need to test the feasibility and acceptability of recruitment, delivery of the intervention and the follow-up of participants within a randomised controlled trial.

## Aim and objectives

Our overarching future aim is to evaluate within a randomised controlled trial, the clinical effectiveness (as measured by tobacco cessation) and cost-effectiveness of a complex intervention of face-to-face counselling coupled with mobile phone messaging delivered to SLT users visiting Indian primary care clinics in addition to routine care provided by the primary care professional against routine care alone. Prior to undertaking a full trial, we aim to develop and finalise the intervention and then test its acceptability and feasibility. Specific objectives of this study are to assess within an exploratory randomised controlled trial, the proportion of:

ll primary care SLT user attendees approached to take part in the trial that consent to randomisation.Those who are randomised to the intervention comply with the intervention.Those who are randomised on whom the follow-up data can be collected.Missing data on all research measures administered at baseline and 3 months, which will be used to assess the primary and secondary outcomes for conducting effectiveness randomised controlled trial in the future.

## Methodology

### Patient and public involvement

The patients and public were involved in the formulation of the study hypothesis from previous research studies.^24 25^ The research questions, design and outcome measures were derived from previous interaction with different stakeholders including patient and public. Tobacco users and other stakeholders (including primary care physicians, counsellors) will be involved in the development of two components of the intervention, that is, face-to-face counselling and mobile phone messages. These will be done by in-depth interviews and focus group discussion in the formative phase of the study (online supplemental appendix A). The summary of the results of the study will be made available to patients and public at the end of the project period.

10.1136/bmjopen-2021-048628.supp1Supplementary data

### Study design

The study will be conducted in two different phases. The first phase is a formative phase (online supplemental appendix A) and the second phase is an exploratory, parallel-group, randomised controlled trial, with pretest and post-test assessments. The duration of the study will be 18 months. The first phase will last for 8 months, whereas the second phase will occur over 10 months (see table 1). The study flowchart is provided in figure 1.

**Table 1 T1:** SPIRIT figure illustrating the phases of CERTAIN trial and data collection time points

	Study period					
	Pre-enrolment	Enrolment	Allocation	Post allocation		Close-out
**Time point**	0	0	0	0	3 months	After 3 months
**Enrolment**						
Eligibility screening		X				
Informed consent		X				
Randomisation to treatment allocation			X			
**Interventions**						
Routine care	X					
Ten-minute face-to-face counselling				X		
Mobile message-based counselling					X	
**Assessments**						
Demographic		X				
Baseline assessment		X				
Mid-line assessment—qualitative assessment at 1.5 months of recruitment					X	
End-point assessment						X
Saliva cotinine assessment						X
Qualitative assessment with drop outs						X
Qualitative assessment with participants who successfully completed the follow-up						X

CERTAIN, Counselling intErvention foR smokeless Tobacco cessAtion in INdian primary care; SPIRIT, Standard Protocol Items: Recommendations for Interventional Trials.

**Figure 1 F1:**
[figure not shown]
Trial schema showing the pathway for patients’ recruitment process in Counselling intErvention foR smokeless Tobacco cessAtion in INdian primary care (CERTAIN) study.

### Study setting

The study will be conducted in urban primary health centres (UPHCs). All UPHCs in Berhampur city of Ganjam district of Odisha will be selected for this study.

### Study population

The study participants will include adult SLT users who visit UPHCs in Berhampur city, Odisha. Participants will be current SLT users (i.e, users in the last 3 months), aged 18 years and above, have a mobile phone with a valid contact number and willing to consent to participate in the study.

Participants below the age of 18 years, who do not have the mental capacity to consent, with illness limiting their adherence and follow-up within the study, will be excluded.

### Interventions

The intervention arm includes routine care (component 1) along with a single 10-min face-to-face intervention based on 5A’s approach (component 2), followed by mobile phone counselling (component 3). The control arm will be the provision of routine care alone (ie, component 1).

Counselling intErvention for smokeless Tobacco cessAtion in INdian primary care (CERTAIN) intervention: the intervention will be a combination of the following components

Component 1 or delivery of ‘routine care’ as delivered by a primary care physician over 1 min to 2 min. This component will be delivered to both the intervention and control arms of the study. This is based on ‘Ask’ and ‘Advice’. Under ‘Ask’, the physician will ask about consumption of SLT and under ‘Advice’, the physician will advise participants about the benefits of complete abstinence in a clear personalised manner.Component 2 will include a single 10-min face-to-face intervention delivered by a practice-based counsellor. This component will include brief standardised advice provided to participants based on 5A’s approach^26^ to tobacco cessation. Under this approach, the counsellor will ‘Ask’ the participants whether they use SLT; ‘Advice’ them on the importance of quitting (following the same script of component 1). Additionally, they will ‘Assess’ their willingness to ‘quit now’; offer them ‘Assistance’ in the form of nicotine replacement therapy and/or provide them with a referral for behavioural support and ‘Arrange’ a follow-up to check on progress. This will conclude with their enrolment to receive component 3—mobile phone intervention.Component 3 will also follow 5A’s approach to tobacco cessation. The intervention will include an initial message after 48 hours of recruitment, to remind them to quit tobacco followed by messages occurring three times a week for the next 3 months. Each follow-up message will offer behavioural messages to support quitting; information about health risks of tobacco use and benefits of quitting and advice on withdrawal symptoms and coping strategies.

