#### Outcomes

The main outcomes expected from this exploratory trial include:

The proportion of all the tobacco users approached who consent to randomisation.The proportion of those randomised who comply with the intervention.The proportion of those randomised on whom follow-up data are collected at 3 months.

We will also assess the feasibility of assessing outcomes of primary interest in the main trial as listed below:

‘Self-reported tobacco abstinence’ of 7 days confirmed by a salivary cotinine test.Self-reported motivation and intention to quit.Cost-effectiveness as cost per disability-adjusted life year (DALY) averted.Cost-effectiveness as cost per quality-adjusted life year (QALY) gained.

The outcomes will be assessed at baseline on recruitment to the study and the end of 3 months. At baseline, sociodemographic details such as age, gender, educational level, marital status, religion, community, and economic status will be recorded. Variables related to tobacco consumption will be recorded, including the number of SLT products per day (frequency) consumed, age of initiation, number of previous cessation attempts and longest period of cessation. The data on quit attempts, the status of tobacco use and challenges will be recorded during baseline and end point. The biochemical validation of self-reported tobacco abstinence for 7 days will be assessed using salivary cotinine at the end of 3 months. The rapid test kit works through visual interpretation of colour developed on the kit and is instant in processing.^27 28^ Participants will be approached by the trial team members to provide a small sample of saliva, which will be collected through passive drooling. Collection, transportation and disposition of the biological samples and the kit will be managed at the study site by the site coordinator and research team. Cotinine is a preferred marker for tobacco use because cotinine stays in the body much longer than nicotine. The presence of cotinine in saliva or urine is a reliable indicator of tobacco use. Cotinine in vivo has a half-life of about 20 hours and lasts for about 3–4 days in the saliva and urine.^29 30^

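### Salivary cotinine cannot confirm abstinence in users of the nicotine replacement therapy offered only to the intervention arm, so the secondary abstinence comparison is biased against the intervention, by an unknown amount

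*Protocol article*

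**What the plan says.** **Treatment (Protocol article, Interventions).** Component 2 goes to the intervention arm only. Its 'Assist' step offers help "in the form of nicotine replacement therapy and/or provide them with a referral for behavioural support". The control arm receives component 1 alone, a contact of 1 to 2 minutes in which the physician asks about use and then "the physician will advise participants about the benefits of complete abstinence in a clear personalised manner". Component 1 has no assistance step and no NRT.

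**Outcome (Outcomes).** Abstinence is a self-report "of 7 days confirmed by a salivary cotinine test". On timing: "The biochemical validation of self-reported tobacco abstinence for 7 days will be assessed using salivary cotinine at the end of 3 months". On the test: "The rapid test kit works through visual interpretation of colour developed on the kit and is instant in processing". On interpretation: "The presence of cotinine in saliva or urine is a reliable indicator of tobacco use". The section adds: "Cotinine in vivo has a half-life of about 20 hours", and puts the time it remains in saliva at roughly 3 to 4 days. No other source of nicotine is mentioned. The end-point items named are quit attempts, tobacco-use status and challenges.

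**Use (Outcomes; Statistical analysis).** Abstinence is first among the outcomes whose assessment is being piloted for the main trial. It is compared between arms by logistic regression, as a secondary analysis.

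**The concern.** The marker chosen to verify the outcome responds to something one arm is given. That cotinine is a metabolite of nicotine from any source is general pharmacology. The article does not say it, although it justifies cotinine by comparing its persistence with that of nicotine. In a trial that offers NRT, a positive test no longer separates continued tobacco use from successful substitution.

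Read as written, an abstainer on NRT who tests positive has a self-report that the test does not confirm. Because the protocol offers NRT in one arm only, the error is differential: it lowers confirmed abstinence among intervention participants and leaves controls largely untouched. Two things are at stake: the between-arm abstinence estimate in this trial, and the soundness of the outcome definition that the trial is meant to try out.

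**Working it through.** **Step 1. The plan's own figure.** The sample size rests on precision for recruitment and attrition. For 20% ± 5 points at 95%: n = 1.96² × 0.20 × 0.80 / 0.05² = 245.9, so 246, in line with the stated 250. For 50% at n = 250 the interval is 0.50 ± 1.96 × √(0.25/250), or 43.8% to 56.2%. The printed upper limit is 57%, a small difference unrelated to this point. No abstinence rate enters, so the total of 250 does not depend on the issue.

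**Step 2. Who is affected.** Three conditions must hold together: the participant has stopped tobacco, is taking NRT, and took it recently enough for cotinine to be present. With the stated half-life of about 20 hours, the fraction remaining after t hours is 0.5^(t/20):

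- 3 days (72 h): 0.5^3.6 = 8.2%
- 4 days (96 h): 0.5^4.8 = 3.6%
- 7 days (168 h): 0.5^8.4 = 0.3%

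This fits the stated 3–4 days. NRT that ended a week before the test would not plausibly explain a positive result, so the date of last use matters. The article gives no cut-off for the kit.

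**Step 3. Size of the bias.** Let q be true abstinence in the intervention arm and u the share of those quitters on NRT within the window. Observed abstinence is q(1 − u). Assume no NRT use among control quitters. Neither q nor u is in the document. The values below are assumptions: q = 20% and control 10%, so the true odds ratio is (0.20/0.80)/(0.10/0.90) = 2.25.

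| u | Observed, intervention | Difference | Observed odds ratio |
|---|---|---|---|
| 0% | 20% | 10 points | 2.25 |
| 10% | 18% | 8 points | 1.98 |
| 20% | 16% | 6 points | 1.71 |
| 25% | 15% | 5 points | 1.59 |
| 30% | 14% | 4 points | 1.47 |
| 50% | 10% | 0 points | 1.00 |

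Example at 25%: 0.20 × 0.75 = 0.15, and (0.15/0.85)/(0.10/0.90) = 1.59.

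If both true rates were 15%, u = 20% would give 12% against 15%, and an odds ratio of (0.12/0.88)/(0.15/0.85) = 0.77 where there is no true difference.

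**Step 4. Bias against sampling error.** With 20% attrition, 125 × 0.80 = 100 per arm are analysed. For 20/100 against 10/100, the standard error of the log odds ratio is √(1/20 + 1/80 + 1/10 + 1/90) = 0.417. The 95% interval around 2.25 is about 0.99 to 5.1. The shifts in Step 3 lie within it. The difference is that sampling error shrinks in a larger trial and this bias does not.

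**The case against.** **The trial is a feasibility study.** Its main outcomes are consent, compliance and follow-up, and abstinence is compared only in a secondary analysis. This stands, and it limits the weight of the point.

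**The size may be small.** NRT is one option within a single 10-minute session, with no supply or duration stated, and the test comes 3 months later. Few quitters may still be using it. This also stands: nothing in the document supports any particular value of u.

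**The text does not say that such participants are failures.** A reader might infer a fixed rule that counts every quitter on NRT as a failure, in one arm only. The article does not go that far. It requires confirmation by cotinine but gives no rule for a self-reported abstainer who tests positive, and it defers a detailed analysis plan. Controls could also obtain NRT elsewhere. What survives is that the article fixes the marker and its interpretation, and that a later plan cannot reclassify anyone if NRT use was never recorded. The questionnaire on healthcare resource use (Economic evaluation) may capture it, but the article does not say so.

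**Relying on self-report creates the opposite bias.** Waiving a positive test for NRT users removes verification mostly in the intervention arm, where participants know they were counselled. Someone using both NRT and tobacco could then count as a success. This stands, and it is why neither classification should be reported alone.

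**Conclusion.** The point holds at moderate severity. As written, the abstinence outcome can misclassify true quitters who used NRT within about 3–4 days of the test. The protocol's own offer concentrates that error in the intervention arm, so the bias runs against the intervention. Under assumed true rates of 20% and 10%, a true odds ratio of 2.25 would be seen as anything from 1.98 (10% of intervention quitters on NRT) to 1.00 (50%). The actual size is unknown. The illustration assumes that every such quitter tests positive and that no control quitter uses NRT.

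A reader might infer two stronger conclusions that the document does not support. One is that the trial fails in its purpose: its feasibility outcomes and sample size do not depend on cotinine. The other is that the main trial will be sized on an effect that is too small: the article says only that this study will inform a larger trial, and nowhere that this estimate will set its size.

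**What to change.** 1. At the 3-month visit, ask participants in both arms about NRT and any other non-tobacco nicotine, with the date of last use, so that use can be matched to the 3–4 day window.
2. Qualify the statement in Outcomes on what cotinine indicates, so that it does not apply to current NRT users.
3. Prespecify and report abstinence two ways: (a) self-report with a negative cotinine test; (b) as (a), but with self-reported abstainers who test positive and used NRT within the window counted as abstinent and flagged as unverified.
4. Report NRT use, and the number of self-reported abstainers with a positive test, by arm.

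The cost is one or two questionnaire items and a few sentences in the outcome definition. The drawback is that (b) rests on self-report for NRT users, mostly in the intervention arm. Versions (a) and (b) should therefore be read as a range. None of this takes a position on whether NRT should be offered.
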